## **9. Study risk pre-assessment and risk management**

### **9.1 Monitoring of adverse events**

All AEs will be managed and reported in compliance with all applicable regulations and will be included in the final Clinical Study Report (CSR).

### **9.2 Definitions of adverse events**

#### **9.2.1 Adverse event (AE)**

Adverse Events, as long as they occur from the first visit planned in the Clinical Trial Protocol/signature of the informed consent (i.e., occurring during the washout period) to the last visit planned in the protocol, are adverse medical events or deterioration of qualifying event. AEs include symptoms (ie, nausea, chest pain), signs (ie, tachycardia, liver enlargement) and abnormal laboratory results (ie, laboratory or ECG abnormalities). AEs can be classified as serious adverse events (SAEs) and non-serious AEs.

#### **9.2.2 Serious adverse event (SAE)**

A Serious adverse event is refers to :

- Results in death, or
- Is life-threatening, or

**Note: The term “life-threatening” in the definition of “serious” refers to an event in which the patient is at risk of death at the time of the event; it does not refer to an event which hypothetically might have caused death if it was more severe.**

- Requires inpatient hospitalization or prolongation of existing hospitalization, or
- Results in persistent or significant disability/incapacity, or
- Is a congenital anomaly/birth defect, or
- Is a medically important event

### **9.3 Recording of adverse events**

Non-serious AE: Only some of the non-serious AEs will be collected from time of randomization throughout the treatment/follow-up periods to the Study Closure Visit. Other non-serious AEs are up to the investigator to decide whether to collect.

SAE: All SAEs will be collected and recorded.

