### **9.5 Obligation of the investigator regarding safety reporting**

#### **9.5.1 Adverse events**

All AEs will be recorded on the corresponding page(s) in the CRF. Whenever possible, symptoms should be grouped as a single syndrome or diagnosis. The Investigator should specify the date of onset, intensity, action taken with respect to Investigational Product, corrective treatment/therapy given, outcome and his/her opinion about whether it is possible that the AE is caused by the study intervention, related to the index stroke, other cause, or intercurrent condition.

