### **(3) Safety Analysis**

Safety events in the two treatment groups will be described based on the SAS dataset. Logistic regression will be used to compare the differences in safety endpoints such as intracranial bleeding events between the two groups. Chi-square test and Fisher's exact test will be used to compare the differences in the incidence of AEs and SAEs between the two groups.

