## **16. Data Security Monitoring**

The data safety monitoring board (DSMB) is established to monitor the safety of participants, protect participants and ensure the integrity of the study. All AEs should be recorded, handled and tracked until they are properly resolved or stabilized. Any SAEs and unexpected events should be reported in a timely manner to the ethics committee in accordance with the relevant provisions, the competent department, the sponsor and the supervisory and administrative departments. The principal researchers should regularly review all AEs and set up meetings to assess the risks and benefits of the study if necessary. An independent data safety monitoring committee will be appointed to review safety data, evaluate the effectiveness of data monitoring, and decide whether to make new proposal.

During the clinical trial, the data of the subjects should be collected anonymously in the CRF. The subjects are identified only by the subject number and the abbreviation of the initials. Due to safety reason and administrative instructions, when the subject's identity is leaked, researchers shall share the responsibility of confidentiality. In the informed consent form, the patient allows authorized research staff, ethics committee, and the authority to refer directly to the relevant original data on the case report (such as the patient's medical file case, booking records, the original laboratory records, etc.). The above personnel shall comply with occupational confidentiality rules and must keep all patient's identity and medical information confidential.

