## 9.5 研究者在安全性报告方面的职责

### 9.5.1 不良事件

从入组第一次访视或签署知情同意书（如：出现在洗脱期）开始，到研究方案最后一次随访结束为止，患者出现的任何 AE，无论其严重程度，是否与研究相关，都应记录在 CRF 相关页面中。在任何可能的情况下，患者出现的症状都应被分组为某个单独的综合征或临床诊断。研究者应具体描述事件发生的时间、事件强度、采取的相应措施、给予的对症治疗、结局以及他/她关于该 AE 是否有可能由研究导致的判断。

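### Non-serious adverse events are partly recorded at the investigator's discretion, against three other protocol sections that cover all AEs, yet AE incidence is tested between arms without restriction to systematically collected events

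*Supplement*

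**What the plan says.** **Recording rules (protocol v7.1).** Section 9.3 sets three levels:
- A subset of non-serious events is collected: "Only some of the non-serious AEs will be collected from time of randomization".
- The remainder is optional: "Other non-serious AEs are up to the investigator to decide whether to collect".
- Serious events are not optional: "SAE: All SAEs will be collected and recorded".

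Three other sections cover every AE. Section 9.5.1: "All AEs will be recorded on the corresponding page(s) in the CRF". Section 16: "All AEs should be recorded, handled and tracked until they are properly resolved or stabilized". Section 9.1: "All AEs will be managed and reported in compliance with all applicable regulations", and it adds that they go into the clinical study report.

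**Tests.** Protocol section 10.3.2 (3) says that chi-square and Fisher's exact tests "will be used to compare the differences in the incidence of AEs and SAEs between the two groups". SAP v2.0 section 13 applies Fisher's exact test to each grouped AE and to the number of AEs or SAEs. It also summarises separately the AEs seen in more than 5% of subjects in either arm.

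**Blinding.** Under protocol section 3.4 the patient and the treating physician know the allocation. In-hospital evaluation by an unaware investigator is required for information related to the study endpoints. Section 8.4 has the day 30, day 90 and 12-month assessments done by physicians blinded to allocation. The schedule in section 8.6 marks AE/SAE collection at 36 hours, at day 7 or discharge, and at those three later visits.

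**The concern.** There are two linked problems. First, the recording rules cannot both be obeyed. A site that follows 9.3 may leave out events that 9.5.1 and section 16 say must be entered, so different sites can comply with different sections.

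Second, the data produced by the optional rule go into between-arm tests. If the threshold for recording a minor event depends on the arm, the test compares recording behaviour as well as harm. The direction cannot be known in advance. Closer observation after a procedure could create an apparent excess with EVT. Treating a minor event as an expected part of the procedure could hide a real one. What is at stake is the credibility of the non-serious and overall AE tables.

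**Working it through.** **1. Can the rules be reconciled by reading?** One might take 9.5.1 to mean that whatever 9.3 selects is entered on the form. The Chinese protocol text does not allow that. Its 9.3 gives the same discretion, yet its 9.5.1 says that any AE, whatever its severity and whether or not related to the study, "都应记录在 CRF 相关页面中" (is to be recorded on the relevant CRF page). The conflict is present in both languages.

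**2. Are the tests limited to events collected alike?** No. Neither protocol 10.3.2 (3) nor SAP v2.0 section 13 restricts the comparison to SAEs or to a prespecified set of AEs.

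**3. Can discretion depend on the arm?** AE recording is not among the tasks that section 3.4 assigns to an unaware investigator, unless the event is an endpoint. Section 9.5.1 asks the investigator to judge whether the study intervention caused the event. Two of the five scheduled AE collections (36 hours, and day 7 or discharge) take place in hospital, and the other three fall at blinded assessments. The exposure is therefore mainly in hospital.

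**4. How large could the effect be?** There is no stated figure to reproduce, because the documents give no AE rates or recording probabilities. What follows is an illustration.

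From the documents: 251 per arm (protocol 10.1) and two-sided 0.05 (SAP section 9). Assumed: a true proportion with any AE of t = 0.40 in both arms; a share m of AE patients with at least one event that must be recorded (an SAE or one of the subset); and a probability r that an AE patient without such an event is recorded at all.

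Recorded proportion = t × [m + (1 − m) × r].

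- m = 0, r = 0.90 v 0.80: 0.40 × 0.90 = 0.36 v 0.40 × 0.80 = 0.32.
- m = 0, r = 0.90 v 0.70: 0.36 v 0.28.
- m = 0.5, r = 0.90 v 0.80: 0.40 × (0.5 + 0.45) = 0.38 v 0.40 × (0.5 + 0.40) = 0.36.
- m = 0.5, r = 0.90 v 0.70: 0.38 v 0.34.

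Rejection probability for the pooled two-proportion z test (equivalent to the uncorrected chi-square test), with d = p1 − p2, mean p̄, s0 = √(2p̄(1 − p̄)/251) and s1 = √((p1(1 − p1) + p2(1 − p2))/251):

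P = 1 − Φ((1.96·s0 − d)/s1) + Φ((−1.96·s0 − d)/s1).

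For 0.36 v 0.32: p̄ = 0.34, s0 = 0.04229, s1 = 0.04225, d = 0.04. The first term is 1 − Φ(1.015) = 0.155 and the second Φ(−2.91) = 0.002, total 0.157. Exact binomial enumeration gives 0.158.

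| Recording of discretionary cases | m | Recorded rates | Chi-square (exact enumeration) | Fisher's exact |
|---|---|---|---|---|
| 90% v 80% | 0 | 36% v 32% | 0.158 | 0.137 |
| 90% v 80% | 0.5 | 38% v 36% | 0.074 | 0.062 |
| 90% v 70% | 0 | 36% v 28% | 0.486 | 0.449 |
| 90% v 70% | 0.5 | 38% v 34% | 0.154 | 0.133 |

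With equal recording in both arms the chi-square figure is 0.05. With m = 0 and true rates from 20% to 50%, the chance runs from 9% to 21% for 90% v 80%, and from 23% to 63% for 90% v 70%. A single AE term that is wholly discretionary behaves like m = 0.

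**The case against.** The case against accepts the textual conflict but disputes its weight, and several of its points stand.

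- **Who records.** A reader might infer that unblinded investigators record the AEs. No section says who does. The treating physician knows the arm, so unblinded recording in hospital is plausible, but it is an inference, and the three later visits use blinded physicians.
- **The missing list.** The Chinese 9.3 speaks of non-serious AEs of interest, and the protocol refers to a CRF, data collection guidelines and a Manual of Procedures that are not part of the supplement. A list may exist there. It can be said only that the protocol and SAP contain none. A list elsewhere would not remove the discretion sentence.
- **Size.** Every rate above is assumed. Taking 16% and 49% as the expected effect would apply recording loss to every AE patient, although SAEs and a subset are always collected. Fisher's exact test, the SAP's method, lowers the figures further.
- **Reach.** A reader might infer that the trial's safety conclusion is compromised. It is not. Symptomatic ICH, any ICH, mortality and hemicraniectomy are defined separately from non-serious AE recording, safety endpoints go to the clinical event committee, and imaging is read by the core laboratory. No stopping or success rule uses non-serious AE counts.

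Selective AE collection can be legitimate. It then needs a fixed list applied alike in both arms and tests confined to that list. The plan shows neither.

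**Conclusion.** The concern holds in a limited form. Section 9.3 contradicts 9.1, 9.5.1 and 16, and the between-arm AE tests are not restricted to uniformly collected events. Because the trial is open-label and blinded in-hospital evaluation is required only for endpoint-related information, recording of optional events may differ by arm and distort the non-serious and overall AE comparisons in either direction. SAEs and the primary and secondary safety endpoints are not affected.

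The size cannot be derived from the documents. Under the assumptions above, the lower ends of the two false-positive ranges (7% and 15%) suppose that half of AE patients have a mandatory event, and the upper ends (16% and 49%) suppose that all recording is discretionary. This is a minor-to-moderate point: it should be corrected, but it does not touch the trial's main efficacy or safety conclusions.

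**What to change.** 1. In section 9.3, delete the sentence that leaves other non-serious AEs to the investigator, and state one recording rule for both arms. The preferable rule is a closed list of non-serious AEs asked about at every visit, plus all SAEs.
2. Amend 9.1, 9.5.1 and 16 to match. Editing 9.3 alone would leave a closed list in conflict with all three.
3. In protocol 10.3.2 (3) and SAP section 13, restrict the between-arm AE tests to that list plus SAEs, and present any other reported AEs descriptively without a test.

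Recording every AE would also end the contradiction. It is more burdensome, because section 9.2.1 counts abnormal laboratory and ECG results as AEs, and it would leave ascertainment with the same clinicians, so differential detection would be reduced but not removed.

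The closed list costs protocol, CRF and SAP wording, a little more data entry for the listed events, and fewer AE terms tested. It needs no extra patients or visits.

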### **9.4 Causal relationship between adverse events and study:**

Attribution of: (1) Definite; (2) Probably; (3) Possibly; (4) Unlikely; (5) Not related; (6) Not applicable.

### **9.5 Obligation of the investigator regarding safety reporting**

#### **9.5.1 Adverse events**

All AEs will be recorded on the corresponding page(s) in the CRF. Whenever possible, symptoms should be grouped as a single syndrome or diagnosis. The Investigator should specify the date of onset, intensity, action taken with respect to Investigational Product, corrective treatment/therapy given, outcome and his/her opinion about whether it is possible that the AE is caused by the study intervention, related to the index stroke, other cause, or intercurrent condition.

#### **9.5.2 Serious adverse event**

For SAEs, the investigator must immediately take corresponding measures:

Immediately notify the representative of the Monitoring Team, send the signed and dated corresponding pages of in the CRF to the representative of the Monitoring Team, and attach a photocopy of all examinations conducted and the examination dates. For laboratory results, include the laboratory normal ranges. The contact information (name, address and fax number) of the representative is on the Clinical Trial Protocol. These measures should be completed no later than **24 hours** after SAE.

Care should be taken to ensure that the patient's identity is protected and the patient's identifiers in the Clinical Trial are properly noted on all copies of source documents provided to the Sponsor.

### **9.5.3 Follow-up and risk management**

The Investigator should take all appropriate measures to ensure the safety of the patients.

Screening of subjects should strictly follow the inclusion and exclusion criteria of the study. If an AE occurs during the study period, relevant evaluations will be performed, including blood routine examination, coagulation, creatinine, hepatic function, renal function, arterial blood gas analysis, ultrasound and computer tomography. Targeted treatment and necessary consultation should be carried out in a timely manner. When dealing with SAEs, it is important to make sure patient's airway is clear, respiration, blood pressure and heart rate is steady.

Notably, the investigator should follow up the outcome of any AEs (clinical signs, laboratory values or other, etc.) until the patient's condition returns to normal or stabilizes. The follow-up will continue even if the patient withdraws from the clinical trial, and the patient will be interviewed by telephone or face-to-face at the scheduled visit time. The monitoring team may request additional visits and investigations.

## **10. Statistical Analysis**

### **10.1 Sample size estimation**

In this study, a multicenter, open, randomized, parallel control design method was used. The primary measure of efficacy was mRS score at 90 days ( $\pm 7$  days) after enrollment (considered as ordered variable). According to the literature data and clinical experts' opinions, the parameters were set as follows: (1) The proportion of mRS score 0-6 in control group was 3%, 4%, 10%, 17%, 16%, 12% and 38%, respectively; (2) The average treatment effect of EVT improved the outcome with the common OR value for improvement of mRS reached 1.73; (3) Two Interim analysis were considered. Adjusted level  $\alpha=0.046$  (two-sided) and power  $1-\beta=0.90$ . (4) The randomization was allocated to the intervention group and the control group in a 1:1 ratio. Based on these parameters, the total sample size was 452. Considering 10% attrition rate,

the final total sample size was 502 cases, 251 cases in each group.

Interim analysis will be conducted when 1/3 (168) and 2/3 (336) of patients have completed 3-month follow-up. The O'Brien-Fleming boundaries will be used at the interim analysis with a two-sided alpha of 0.0002 (stage 1), 0.0123 (stage 2) and 0.046 (stage 3, final analysis).

The PASS software (NCSS, LLC, version 11) was used to calculate the sample size.

## **10.2 Data collection and entry**

Paper-based CRF and electronic data capture (EDC) system will be used for data collection and input. All the content required by the protocol in the system must be filled, the unfilled content should be explained, and the reason needs to be marked in the EDC system.

### **10.2.1 Paper-based CRF filled out by the investigator**

Site investigators should use black or blue-black recording pens to fill out the paper-based CRF neatly and clearly to ensure that the data is clear and readable. If the paper-based CRF information needs to be modified, it should not be altered or overwritten. The correct information should be written next to the original information, signed and dated by the person who modified it. The clinical research monitor (Clinical Research Associate, CRA) will review the completeness and accuracy of the CRF and guide the investigator to make necessary corrections and supplements.

### **10.2.2 Data entry to the EDC system by CRC**

After the paper-based CRF is completed, the Clinical research coordinator (CRC) will input the content of the paper CRF into the EDC system.

### **10.2.3 Submission to the EDC system after the approval of the investigator**

The paper-based CRF is will be submitted after the investigator has approves it. After the data is submitted, all data revisions and feedback are carried out through the EDC system. If the EDC system has submitted a form that needs to be modified, contact the CRA of this center.

After the CRA opens the form, the investigator can guide the CRC to modify the data in EDC system.

#### **10.2.4 Data monitoring and query by CRA via EDC**

#### **10.2.5 Data exportation from the EDC system**

After the data from the EDC system is exported to the database, it will be proofread by the data administrator. Obvious errors will be corrected by the data administrator. Other errors or missing values will be filled in the data query form, and the query form will be sent to the participating center for solutions through email, express, telephone or WeChat.

The participating centers are responsible for correcting the data in the EDC system after verifying the original data and related information. Site investigators must answer these queries by verifying or modifying relevant information or data.

### **10.3 Statistical considerations**

This section is an overview of the statistical considerations. It provides the general specifications for the analysis of the data to be collected and presented in the CSR. A final Statistical Analysis Plan (SAP) will be issued prior to database lockdown and before code breaking. The SAP will define all “pre-specified, planned analyses.”

All programming will be performed using SAS Version 9.4.

#### **10.3.1 Analysis sets**

##### **(1) Full Analysis Set (FAS):**

Based on the principles of the Intent-to-Treat (ITT) analysis, all randomized subjects, either treated with medication or with EVT will be included in the FAS. The primary efficacy endpoint analysis of this study will be performed on the FAS.

##### **(2) Per Protocol Set (PPS)**

The PPS is a subset that includes all subjects who were treated with the treatment

assignment to which they were randomized and there are no clinically meaningful deviations from the protocol. Severe deviations from the protocol will be finally defined during the data auditing process, including but not limited to the followings:

- 1) The subject is not in line with the inclusion criteria.
- 2) There are other treatments that potentially confound the appraisal of efficacy of the planned treatment.
- 3) Poor compliance.
- 4) Follow-up interval exceeds the required time window.

Secondary analysis will be conducted on the PPS. If its result are not consistent with that of the FAS, a detailed analysis to examine the difference(s) will be required.

### **(3) Safety Analysis Set (SAS)**

The SAS consists of all subjects who received treatment with at least one evaluation of the safety outcome.

## **10.3.2 Statistical considerations**

### **(1) Baseline characteristics comparisons**

T-test or Wilcoxon rank sum test will be used for comparison between continuous variables, and Chi-squared tests, Fisher's exact test or Wilcoxon sum rank test will be used for comparison between categorical variables.

### **(2) Efficacy Analysis**

Primary efficacy endpoint: Based on an ITT basis, an ordinal logistic regression model is used to calculate the common odds ratio between the two treatment groups. All statistics will be two-sided with  $p < 0.046$  considered significant.

Secondary Efficacy Analyses: Endpoints including the 90-day mRS 0-2 will be analyzed using a binary logistic regression model. The infarct core volume change from baseline will be analyzed using student t-test or Wilcoxon rank sum test as appropriate.

### **(3) Safety Analysis**

Safety events in the two treatment groups will be described based on the SAS dataset. Logistic regression will be used to compare the differences in safety endpoints such as intracranial bleeding events between the two groups. Chi-square test and Fisher's exact test will be used to compare the differences in the incidence of AEs and SAEs between the two groups.

### **(4) Subgroup analysis**

The mRS at 90 days will be presented for each level of the covariates listed below:

- (1) Age ( $< 70$  vs.  $\geq 70$ )
- (2) Weak-up stroke or not
- (3) Last known well to randomization time ( $< 6h$  vs.  $\geq 6h$ )
- (4) Stroke severity before randomization (NIHSS $<16$  vs. NIHSS $\geq 16$ )
- (5) IV thrombolysis or not
- (6) Occlusion site (ICA vs. M1 segment)
- (7) Ipsilateral carotid artery occlusion or not
- (8) ASPECTS ( $< 3$  points vs.  $\geq 3$  points)
- (9) Infarct core volume ( $< 70ml$  vs.  $\geq 70ml$ )
- (10) Etiological stroke subtype (Cardiac embolism vs. large artery atherosclerosis)

## **10.4 Interim analysis**

Interim analysis will take place when 1/3 (168 cases) and 2/3 (336 cases) have completed 3-month follow-up. The O'Brien-Fleming boundaries will be used at the interim analysis as follows:

There are no established techniques for the assessment of interim trial efficacy boundaries using an ordinal logistic regression model (proportional odds model). Instead, we will revert to a simple dichotomous analysis of the mRS score at 0-2 defined at 90 days from randomization. The Z-statistic for this analysis shall be derived from the normal approximation of the binomial distribution as an unadjusted two-sample test of proportions. For an RCT comparing two treatment groups with respect to a binary outcome and two interim analysis, corresponding

significance levels based on the O'Brien & Fleming boundary are two-sided 0.0002 (stage 1), 0.0123 (stage 2) and 0.046 (stage 3, final analysis).

With the result of interim analysis, DSMB will make the decision to continue or halt the study according to the test boundaries. The study will stop prematurely for futility if the result from the interim analysis indicate that we can't achieve an effective conclusion with the current sample size. Premature stopping for early success will be achieved if the interim analysis result has already proved the effect of intervention at significance level. Otherwise, the study will be continued until the predefined termination date. In interim analysis, the final sample size is allowed to be adjusted if the estimation of the primary outcome is drastically different from the actual data.

